### Feasibility Study

A voluntary feasibility study was conducted during the 2018-2019 school year in six public primary and secondary schools in the Madrid region to test a preliminary version of the LINKlusive web-based intervention program. The intervention was feasible and well accepted by participants. Teachers provided feedback on the materials and the online assessment and intervention platform and collected opinions from students. Teachers suggested several modifications to the report provided by the platform to form the heterogeneous student groups required for delivering the educational program and to the teaching units for secondary education students to suit better their cognitive and social developmental level. After the feasibility study, we implemented some modifications to the report for working with heterogeneous class groups, so that the teacher can request a recombination of the groups if the original proposal is not satisfactory, and we revised the didactic units for secondary education per the teachers' suggestions.

### Study Procedures

Pupils in both groups complete all bullying (i.e., peer- and self-reported measures) and self-reported mental health and quality of life assessments on the web-based platform (www.sociescuela.es) at baseline (January 2019), study endpoint (May-June 2019), and one year after the endpoint (initially expected in May-June 2020) in both treatment groups using tablets (see Figure 1). Due to the impact of the COVID-19 pandemic in Spain, the 1-year follow-up assessment has been postponed until the 2020-2021 school year. The intervention in the experimental group took place between February and May 2019.

Teachers are available in the classroom during assessments for technical questions or clarification. For children with SEN who have comprehension difficulties, class teachers may also supervise data collection, and questionnaires and assessment methods may be adapted as required (e.g., use of visual support strategies for children with autism).

In the experimental group, additional information is collected from families and teachers through the online platform to monitor the use of designated training content. Teachers also report on the degree of completion of the school-based educational program, adherence to intervention recommendations in identified bullying cases, and their satisfaction with the program.

In experimental schools, researchers held two meetings with teaching staff, one before initiation of the intervention to explain the study procedures and present the online platform, and another visit after completion of the intervention to collect feedback. Researchers were also available by phone or e-mail for technical requests or questions regarding delivery of targeted intervention plans in particular situations.

### Measures and Instruments

The main outcome measure of the trial is peer-reported bullying victimization (i.e., at least two peer nominations on the Sociescuela victimization subscale, see below for further details). The study also assesses the following outcome measures: peer-reported bullying perpetration, self-reported victimization and bullying perpetration, mental health symptoms (e.g., internalizing and externalizing symptoms, psychotic-like experiences), self-esteem, and quality of life (see Table 1 for a summary of the variables assessed and the instruments used in the study).

**Table 1 T1:** Variables and instruments used in the LINKlusive study.

**Variable**	**Assessment method**	**Instrument**
Peer-reported bullying victimization and perpetration	Peer-report, social network analysis within the classroom	Sociescuela (46)
Self-reported bullying victimization and perpetration	Self-report, questionnaire	*Ad hoc* questionnaire [adapted from (68)]
General psychopathology, internalizing and externalizing psychopathology	Self-report, questionnaire	Strengths and Difficulties Questionnaire and corresponding subscales (70)
Psychotic-like experiences	Self-report, questionnaire	Community Assessment of Psychic Experiences (CAPE-15) (81, 82)
Self-esteem	Self-report, questionnaire	Rosenberg self-esteem scale (83)
Quality of life	Self-report, questionnaire	KIDSCREEN-10 (86)

*Students completed all assessments through an online platform using tablets. Demographic variables were collected through an ad hoc questionnaire. Teachers also completed questionnaires regarding students with special educational needs, concomitant anti-bullying interventions conducted in schools, and adherence to the LINKlusive intervention components in the intervention group*.

#### Demographic and Social Variables

Student demographic data (age, sex) are collected through the online platform. The socio-economic level of the participating schools will be calculated based on statistical data for the district or town where the school is located published by the regional government of Madrid and the Spanish National Statistics Institute.

#### Students With Special Educational Needs

Additional variables regarding the numbers of pupils with SEN, availability of specific resources for children with neurodevelopmental disorders at each school, and diagnoses for which the pupils receive educational support are collected from the class teachers through the online platform.

#### Bullying Assessment

As recommended by most authors, we included both peer- and self-reported measures of bullying victimization and perpetration in the study. Previous studies have found a low correlation between self- and peer-reported methods in both victims (62–66) and perpetrators (63). Despite the fact that there has been more research using self-reports, some authors suggest that peer-report could enable a more precise identification of bullying situations (63), as it may reduce measurement errors and increase reliability since it is based on multiple informants, while it may also help to overcome the secrecy and code of silence that often surrounds bullying situations (67).

##### Peer-Reported Bullying Victimization and Perpetration: Social Network Analysis

Peer-reported bullying behavior was assessed by analyzing the group structure and social networks within the classroom, where most bullying cases occur (46). This model assumes that bullying is influenced by the social context and not only by the bully-victim interaction. In light of this, Sociescuela is a bullying assessment instrument that uses technique borrowed from social-network analysis for developing social maps (social cognitive mapping, NEGOPY). The rationale and validation data of Sociescuela have been extensively reported elsewhere (46). In brief, students provide peer nominations and ratings of their social preferences, thus providing an accurate picture of the social structure of the class. The instrument is composed of three subscales: (i) a victimization subscale (composed of three items assessing physical, verbal, and relational victimization), (ii) an acceptance subscale (composed of five items based on sociometry assessing positive and negative peer nominations), and (iii) a subscale of perceived attributes (12 items assessing prosociality, withdrawal, and aggressiveness). The subscale of perceived attributes helps identify different victim profiles (e.g., active vs. passive). The instrument also enables identification of bullying perpetrators. The instrument has been validated in a large sample of Spanish children and adolescents and found to have appropriate psychometric properties (46). For purposes of this study, we identify bullying victims and perpetrators as those who receive at least two nominations by their peers as either victims or perpetrators in any of the items of the victimization subscale (62).

Using measures of friendship and frequent interaction, as well as social cognitive mapping, a graphical structure of the group structure is created, which helps identify social groups within the classroom and determine who are not members of any social group, and thus potentially at high risk for peer rejection or victimization (see Figure 2 for an example). This provides additional information on groups of friends in the classroom, peer support for bullies and victims, and the degree of bystander involvement in the bullying situation, thus enabling implementation of targeted or personalized interventions and peer support strategies (46).

##### Self-Reported Bullying Victimization and Perpetration

Peer-reported bullying assessment was complemented by an additional self-reported record of bullying victimization and perpetration experiences using a specifically designed questionnaire composed of 16 items assessing the intensity and frequency of social, verbal, physical, and cyber bullying, and one global item. This questionnaire is based on customary bullying definitions and classifications (1) and previous questionnaires used in other bullying prevention programs (e.g., KiVA) (68) and has previously been used and validated in Spanish students (53).

#### General Psychopathology

General psychopathology is assessed using the Spanish version of the Strengths and Difficulties Questionnaire (SDQ) (69). For purposes of this study, we are using the self-report version of the scale (70). The scale includes five subscales assessing the following dimensions in children and adolescents: emotional symptoms, conduct problems, hyperactivity/inattention, peer relationship problems, and prosocial behavior (i.e., positive social skills). Additionally, scores may also be calculated for two broader subscales assessing internalizing and externalizing symptoms (71). Mean total difficulty scores have shown good predictive validity of clinician-rated mental disorders, with no systematic tendency toward under- or overestimation (72). Depressive symptoms were assessed using nine selected items on the Major Depression Disorder subscale of the Revised Child Anxiety and Depression Scale, which measures child-reported depressive and anxiety symptoms with good validity and reliability (73).

#### Psychotic-Like Symptoms

Psychotic-like experiences are assessed with the Community Assessment of Psychic Experiences (CAPE). The CAPE is a self-report questionnaire that assesses frequency and distress associated with psychotic-like experiences in the general population across three dimensions (positive, negative, and depressive) with good internal consistency and validity (74, 75). It is also considered a valid measure of the extended psychosis phenotype (76). Recently, the positive dimension has been tested as a potential screening tool for young individuals at high-risk for psychosis (77). The CAPE has previously been used in non-clinical samples of adolescents, with appropriate validity (78–80). For purposes of this study, we used the Spanish version of the CAPE-P15 (81), which includes 15 items that assess the positive symptom dimension with good internal consistency (81, 82).

#### Self-Esteem

Self-esteem is assessed with an adapted version of the Rosenberg self-esteem scale (83). The Rosenberg scale is a self-report questionnaire that assesses self-esteem with good internal consistency and test-retest reliability (83). For purposes of this study, we are using a 10-item adapted version of the scale after rephrasing some items on the original scale for use in child and adolescent samples. This version has previously been validated in Spanish children and adolescents and found to have good psychometric properties (84).

#### Quality of Life

Health-related quality of life is assessed with the Spanish version of the KIDSCREEN-10. The KIDSCREEN (with self-report and proxy versions consisting of 52, 27, and 10 items) assesses quality of life according to the young person's mental, physical, and social wellbeing. It was developed and validated for children and adolescents 8-18 years of age in 13 EU countries between 2001 and 2004 (85). The KIDSCREEN-10 is based on a Rasch analysis of the KIDSCREEN-27 version and shows adequate internal consistency, validity, and test-retest reliability (3, 86).

#### Concomitant Intervention and Adherence to Intervention Guidance

The following information is collected through questionnaires specifically designed for the study: additional anti-bullying policies and activities available at all the participating schools, as well as program completion (e.g., proportion of teachers and parents completing the training online, number of classrooms participating in the intervention at each school, number of hours of the educational program completed by each participating classroom) and adherence to intervention recommendations (i.e., adherence to recommendations included in the personalized plans) in the intervention group schools. Students and teachers were asked online how many sessions of the educational program they had completed. Likewise, during the visit to schools after implementation of the intervention program, the researchers collected information on the number of sessions that the teachers had completed in each class group and contrasted this information with that provided by the school management team. As for families, the teaching units had a specific access link for each educational center to record the number of users who accessed each session and the time spent on the training. Based on these data, an adherence score will be calculated for each experimental school.

### Statistical Analyses

#### Sample Size Calculation

Based on an estimated bullying prevalence rate of 3.8% in the largest study conducted in a representative sample of the Spanish adolescent population to date (53), along with data suggesting 20-50% reductions in bullying rates with previous effective interventions (17), and an estimated population sample size of 100,000 students, a sample size of [388 to 2148] students would enable us to detect absolute reductions in prevalence rates of [0.8 to 1.9%] with a power of 80% and a significance level of 95%. In light of potential selection bias, we used a standard mean estimation of the uncertainty coefficient and intragroup correlation, and we duplicated this sample size up to [776 to 4,296] pupils to minimize the risk of a type-I error. To reach an approximate sample size of 4,200 pupils, twenty schools need to be randomized 1:1. This will yield a total of approximately 200 classrooms.

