## Introduction

Bullying is defined as deliberate aggressive behavior inflicted upon a young person by one or more of their peers, repeated over time, and involving a power imbalance favoring the perpetrator(s) (1). There is increasing recognition of bullying as a major public health concern in recent years (2). Approximately 10–25% of children and adolescents have experienced bullying in their lifetime (3, 4). Exposure to bullying in childhood has been associated with a wide range of lifelong adverse health and social outcomes (5–9). For instance, bullying victims show increased risk for anxiety, depressive, and psychotic disorders, poorer physical health, and suicidality both in the short- and long-term, along with poorer educational and vocational outcomes in adulthood (10–15). Several school-based interventions have shown effectiveness in reducing bullying rates by about 20% (16–19). Although individual effect sizes are in the small to moderate range, considering the global prevalence of bullying, the population impact number of these interventions seems compelling (19).

Previous health economic analyses suggest that anti-bullying interventions are also cost-effective, considering the medium- and long-term consequences and the indirect costs (20–22). A recent cost-effectiveness analysis of the Finnish KiVA program reported estimated net savings of more than $3,000 per pupil for a cohort of 200 pupils followed through age 50 (21). However, many of these interventions incur high short-term economic costs and require important time investment by teachers and pupils, thus potentially reducing their applicability in some contexts, especially in low- or medium-income countries. Sustainability of conventional anti-bullying interventions has also been limited so far, with rates of school participation decreasing over time (23). Digitally assisted interventions could help to address some of these limitations and decrease costs by reducing personnel effort and increasing the reach and homogeneity of interventions across settings (24), as previously suggested for other psychosocial or psychological therapies (25–27).

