### School Recruitment

Figure 1 shows the flowchart for the selection of schools. Schools were selected from among publicly funded primary and secondary schools enrolling youth with SEN in mainstream classrooms in the Madrid region (*n* = 1,882). Inclusion criteria were as follows: (i) at least one previous assessment of bullying with Sociescuela in the past three years, (ii) peer-reported bullying victimization rates of at least 5% in the latest available assessment with Sociescuela, (iii) only one assessment of bullying prevalence using Sociescuela within the past 3 years (in order to have a previous measure of bullying victimization rates, but minimize previous exposure to the tool), and (iv) for primary schools, presence of specific resources for children with neurodevelopmental disorders (i.e., specific classrooms). The latter criterion was used to enrich the sample for children with neurodevelopmental conditions and accounts for the fact that primary schools in the Madrid region are increasingly incorporating so-called “neurodevelopmental disorder classrooms” or “ASD classrooms.” Therefore, students with SEN due to ASD and other neurodevelopmental conditions mainstreamed in regular schools have been preferentially assigned to schools that have such resources in the past few years. These classrooms, which enroll a maximum of 5 students per class, are usually staffed by a teacher specializing in therapeutic pedagogics or speech-language therapy and a social integration technician. Students with SEN enrolled in these classrooms spend between one- and two-thirds of the time with their peer group in their regular classroom and receive complementary pedagogic and social support through specific activities in the specialized support classroom during the remaining school hours. They also receive support to facilitate integration into the regular classroom as well as during unstructured activities such as recess.

This selection process yielded a final sample size of *n* = 29 schools (*n* = 12 primary and *n* = 17 secondary schools).

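### The stated 388 to 2,148 students do not give 80% power for a between-arm reduction of 1.9 to 0.8 points; both figures match a one-sample precision formula with no power term

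*Protocol article*

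**What the plan says.** Under Sample Size Calculation, the protocol article starts from an "estimated bullying prevalence rate of 3.8" per cent and cites "20-50% reductions in bullying rates with previous effective interventions". It adds "an estimated population sample size of 100,000 students" as a further input and concludes that "388 to 2148] students would enable us to detect absolute reductions in prevalence rates of [0.8 to 1.9%] with a power of 80" per cent. The error rates are given as "with a power of 80% and a significance level of 95" per cent, which I read as a 5% alpha; sidedness is not stated.

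The range is then doubled to 776 to 4,296 pupils. The reasons given are selection bias, an uncertainty coefficient, intragroup correlation and type I error; no ICC value is given. The working target is about 4,200 pupils in 20 schools randomised 1:1.

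The Abstract gives the primary objective as a between-arm comparison of peer-reported victimization at the end of the intervention. Measures and Instruments defines that outcome as binary (at least two peer nominations).

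**The concern.** A trial comparing two arms at a prevalence near 4% cannot normally detect a difference of under one point with about 2,000 pupils, so the stated range looks too small by a large factor. The size of the student population also has no role in a two-arm superiority test, though it does in a survey-precision calculation.

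At stake is how the result will be read. The Discussion relies on the power calculation for the main outcome in the whole sample and raises insufficient sample size only for pupils with special educational needs. A reader would take a null result as coming from a trial with 80% power for reductions as small as 0.8 points.

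**Working it through.** **Inputs from the article.** Control prevalence p = 0.038; differences d = 0.019 and 0.008; population N = 100,000; power 80%; alpha 5% (taken as two-sided); 20 schools, 1:1, about 4,200 pupils, hence 2,100 per arm and 210 per school.

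**1. Reproducing the stated figures.** Precision of one proportion with a finite-population correction:

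n0 = 1.96² × p(1 − p) / d², n = n0 / (1 + (n0 − 1)/N)

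- d = 0.019: n0 = 389.0, n = 387.5, rounded up to 388.
- d = 0.008: n0 = 2,194.2, n = 2,147.1 (2,147.2 with z rounded to 1.96), rounded up to 2,148.

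Both endpoints match. The formula has no power term and no second arm. None of the power-based variants tried reproduces either endpoint: two proportions (one- and two-sided, per arm and total, with and without continuity or finite-population correction), unpooled variance, arcsine, and a one-sample test with 80% power. That last test gives 664 and 4,198 two-sided.

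**2. Size needed for the between-arm comparison, no clustering.**

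n per arm = [1.96 √(2p̄q̄) + 0.842 √(p1q1 + p2q2)]² / (p1 − p2)²

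- 3.8% vs 1.9%: (1.96 × 0.2353 + 0.842 × 0.2349)² / 0.019² gives 1,203 per arm, 2,406 in total (stated: 388).
- 3.8% vs 3.0%: (1.96 × 0.2563 + 0.842 × 0.2562)² / 0.008² gives 8,055 per arm, 16,110 in total (stated: 2,148).
- 3.8% vs 3.04%, an exact 20% reduction: 8,976 per arm, 17,952 in total.

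**3. Power of the stated sizes, no clustering.**

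Power = Φ{[(p1 − p2)√n − 1.96 √(2p̄q̄)] / √(p1q1 + p2q2)}, n per arm

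| Stated size and target | Read as total | Read per arm (equals the doubled total) |
|---|---|---|
| 388, for 1.9 points | 20% | 36% |
| 2,148, for 0.8 points | 17% | 30% |

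One-sided testing at 5% raises the per-arm column only to 48% and 42%.

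**4. Power of the planned 4,200 pupils.** The article gives no ICC, so the values below are assumptions. Design effect = 1 + 209 × ICC; effective n per arm = 2,100 / design effect.

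| School ICC (assumed) | Design effect | Power, 0.8 points | Power, 1.9 points |
|---|---|---|---|
| 0 | 1.00 | 30% | 96% |
| 0.0048 | 2.00 | 17% | about 75% (74.5%) |
| 0.01 | 3.09 | 13% | 56% |
| 0.02 | 5.18 | 9% | 37% |

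The second row treats the article's doubling as a design effect of 2, which implies ICC = 1/209. The smallest reduction detectable with 80% power is about 1.5 points with no clustering and about 2.0 points at a design effect of 2.

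Power for 1.9 points is 80% when 2,100 / design effect = 1,203. That is a design effect of 1.746, or an ICC of 0.746 / 209 ≈ 0.0036.

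**The case against.** The article names no formula, so the one-sample origin is an inference. That stands, but the conclusion does not depend on it: steps 2 and 3 hold however the figures arose.

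The trial was planned for about 4,200 pupils, not 388 or 2,148, and without clustering that number has 96% power for 1.9 points. This also stands, and it rules out saying that the trial lacks power over the whole range. It does not help the 0.8-point end. Method of Randomization and Allocation Concealment expects about 4,500 pupils, but 2,250 per arm gives only about 32% there.

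The Discussion already warns that low baseline prevalence may hide an effect. That gives some caution about a null result but leaves the power claim uncorrected.

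Four stronger readings are tempting, and the documents do not support them:

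- *The trial had under 20% power for 0.8 points.* This requires a design effect near 2. The article gives no ICC and does not call its doubling a design effect.
- *The 3.8% is a self-report figure and so does not fit a peer-reported outcome.* The article cites the same source both for the self-report questionnaire and for victims and perpetrators sharing a class, and never says how the 3.8% was measured.
- *The entry criterion of "peer-reported bullying victimization rates of at least 5% in the latest available assessment with Sociescuela" shows that 3.8% is too low.* The criterion concerns one past assessment, and schools selected on a high value may regress toward the mean. The Discussion reports relatively low baseline rates. Even at 5%, a 20% reduction would have about 35% power with no clustering and 20% at a design effect of 2.
- *The 20-50% range contradicts the Introduction.* The Introduction says "Several school-based interventions have shown effectiveness in reducing bullying rates by about 20" per cent, which lies inside the openly stated range, and the planned size follows the 20% end.

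**Conclusion.** The power statement is wrong as written. The stated sizes fall short of the two-arm requirement by a factor of about 6 at 1.9 points (2,406 / 388) and 7.5 at 0.8 points (16,110 / 2,148). They give 17% to 36% power in two-sided testing, whether read as totals or per arm.

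For the planned 4,200 pupils, power for 0.8 points is at most about 30%. Power for 1.9 points runs from 96% with no clustering to 37% at an ICC of 0.02, and drops below 80% above an ICC of about 0.0036. These figures assume two-sided 5% testing, 3.8% in the control arm, equal school sizes of 210 and a normal approximation. With only 20 schools, a t reference with 18 degrees of freedom lowers them somewhat: at a design effect of 2, to about 16% and 70%.

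The error concerns a stated figure, so it is not a matter of detail that an article would leave to a fuller document.

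**What to change.** Withdraw the claim of 80% power for reductions of 0.8 to 1.9 points. Keep the existing calculation visible, since it records how the size was chosen, and say that it does not size a two-arm comparison. Beside it, report a two-proportion cluster-trial calculation for the fixed 20 schools and about 4,200 pupils. Label it retrospective, because Trial Status shows that the post-intervention assessment is complete.

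The new calculation should give, across a stated range of school ICCs:

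- power for a 20% and for a 50% relative reduction;
- the smallest reduction detectable with 80% power.

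It should use 3.8% and the enrolled schools' own Sociescuela rate as alternative control prevalences. The Discussion should then state that the main comparison has limited power for a reduction near 20%.

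The cost is one recalculation and some rewording, with no additional pupils. The stated power becomes less favourable.

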## Methods and Analysis

### Study Design and Setting

This study was a school-based, parallel, cluster randomized controlled trial conducted in publicly funded primary and secondary schools in the Madrid region. The clustering units for the study were schools. See Figure 1 for further details of the study design.

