### Method of Randomization and Allocation Concealment

Multi-stage cluster sampling was done among publicly funded schools in Madrid. In a first stage, we selected all schools fulfilling the abovementioned inclusion criteria. In a second stage, these centers were randomized 1:1 to the intervention and control groups. Ten schools (5 primary schools and 5 secondary schools) were offered participation in each arm of the trial, with a list of back-up schools in case of refusal to participate (2 primary schools and 7 secondary schools). This process would enable participation of about 96 classrooms in each cluster, including about 4,500 students overall (mean number of students per classroom is 23 in primary schools and 25 in secondary schools). Due to the study design, allocation could not be concealed, and the study was not blinded to participating schools or researchers. Psychological and bullying assessments were based on student reports (self-report or peer-report) on an online platform, with students unaware of the study hypotheses and no direct assessments of the outcome measures by members of the research group.

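### Doubling the sample is wrongly credited with limiting type-I error, covers a school ICC of at most about 0.0048, and does not deliver the stated 80% power

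*Protocol article*

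**What the plan says.** Under Sample Size Calculation, the protocol article starts from an assumed prevalence ("Based on an estimated bullying prevalence rate of 3.8"%) and from "20-50% reductions in bullying rates with previous effective interventions". It then states that "a sample size of [388 to 2148] students would enable us to detect absolute reductions in prevalence rates of [0.8 to 1.9"%. It attaches 80% power and a 95% significance level to that claim. Citing possible selection bias, and mentioning an uncertainty coefficient and an intragroup correlation without values, it continues: "we duplicated this sample size up to [776 to 4,296] pupils to minimize the risk of a type-I error". The number of schools follows from the pupil target: "To reach an approximate sample size of 4,200 pupils, twenty schools need to be randomized 1:1".

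Study Design and Setting fixes the level of clustering: "The clustering units for the study were schools". Planned Analyses specifies a mixed model with school, classroom and student levels.

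**The concern.** Three things do not fit together.

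- **The reason for the doubling.** Enrolling more pupils does not lower the type-I error rate. In a cluster trial, that rate depends on whether the analysis accounts for the clustering. The design-effect inflation restores power.
- **The size of the doubling.** The allowance that a cluster trial needs depends on cluster size and on the ICC at the level randomised. The text links the factor of 2 to neither.
- **The starting figures.** Sizes of 388 and 2,148 look far too small for an 80%-power comparison of two arms at a prevalence of 3.8%.

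At stake is how the primary result will be read. The limitations paragraph in the Discussion says that the power calculation was done for the main outcome in the whole population, and it offers a floor effect as a possible reason for a null result. If power was low by design, a null result could be misread as evidence of no effect.

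**Working it through.** **Inputs from the protocol article.** Control prevalence 3.8%; relative reductions of 20% to 50%; absolute reductions of 0.8 to 1.9 points; population 100,000; power 80%; the 95% significance level read as two-sided alpha 0.05; 4,200 pupils; 20 schools, 1:1. **Assumed here:** equal school sizes, and an ICC range, because the article gives no ICC.

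**1. The plan's own figures.** The doubling is exact: 2 × 388 = 776 and 2 × 2,148 = 4,296. The base sizes reproduce from the single-proportion precision formula with finite-population correction, n = N z² p(1−p) / [d²(N−1) + z² p(1−p)], with N = 100,000, p = 0.038 and z = 1.96:

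- d = 0.019 gives 387.5, so 388.
- d = 0.008 gives 2,147.2, so 2,148.

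This formula has no power term and no second arm.

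**2. The base as a two-arm comparison.** Per arm, n = [1.96√(2p̄(1−p̄)) + 0.842√(p₁(1−p₁) + p₂(1−p₂))]² / (p₁−p₂)², two-sided, without clustering:

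- 3.8% v 1.9%: 1,203 per arm, 2,406 in total.
- 3.8% v 3.0%: 8,055 per arm, 16,110 in total.
- 3.8% v 3.04% (exactly 20%): 8,976 per arm, 17,952 in total.

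One-sided totals for these three are 1,896, 12,690 and 14,142, so sidedness does not explain the gap.

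**3. What a factor of 2 covers.** With m = 4,200/20 = 210, set 1 + (m−1) × ICC = 2. Then ICC = 1/209 = 0.0048. With m = 214.8 (4,296 pupils) it is 0.0047.

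**4. Power that the design gives.** DE = 1 + 209 × ICC; SE = √{DE × [p₁(1−p₁) + p₂(1−p₂)] / 2,100}; power from the non-central t with 20 − 2 = 18 df (critical value 2.101).

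Example at ICC 0.0048 for 3.8% v 1.9%: SE = √[2.00 × (0.036556 + 0.018639)/2,100] = 0.00726. The non-centrality is 0.019/0.00726 = 2.62, and power is 70%.

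| ICC | DE | Effective N | Power, 3.8% to 1.9% | Power, 3.8% to 3.04% | Reduction detectable at 80% power |
|---|---|---|---|---|---|
| 0.0048 | 2.00 | 2,097 | 70% | 15% | 2.11 points |
| 0.005 | 2.05 | 2,054 | 69% | 14% | 2.13 points |
| 0.01 | 3.09 | 1,359 | 51% | 11% | 2.52 points |
| 0.02 | 5.18 | 811 | 34% | 8% | 3.08 points |

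The detectable reduction d solves d = (2.101 + 0.862) × SE. A reduction of 3.08 points is 81% of 3.8%. With no clustering (DE = 1), power for 3.8% to 3.04% is about 25%.

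**5. Where the shortfall arises.** At ICC 0.0048 the doubling pays for clustering exactly, yet power is 70%. That gap comes from the base: 2 × 2,406 = 4,812 pupils would be needed, against 4,200. A normal approximation gives about 74%, and the 18 df take it to 70%. On the base of 2,406, 4,200 pupils leave room for a design effect of 4,200/2,406 = 1.75, an ICC of 0.75/209 ≈ 0.0036.

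**The case against.** The best defence is that 0.0048 is not the plan's number. The text gives selection bias, an uncertainty coefficient and intragroup correlation together as grounds for the doubling, and never calls it a design effect. That stands, but it cuts the other way: whatever share was meant for selection bias leaves less for clustering, so 0.0048 is an upper limit. The ICC value may also be in the full protocol, which is not shown; its absence from an article is not the fault raised here.

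On the base of 388, 4,200 pupils would tolerate an ICC of about 0.047, since (4,200/388 − 1)/209 = 0.047. But 388 is not a two-arm, 80%-power size. Referred to classrooms of about 21 (4,200/200), a factor of 2 matches an ICC of 1/20 = 0.05, but schools were randomised.

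Power also depends on prevalence. Schools needed a latest rate of at least 5% to be eligible, and at 5% control prevalence and ICC 0.005, power for a 50% reduction is about 81%. The plan's own figure is 3.8%, however, and its limitations report relatively low baseline rates.

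A reader might infer more than the documents support:

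- **That the true ICC exceeds 0.005, so the allowance is known to be too small.** No document gives an ICC; 0.01 and 0.02 are assumptions.
- **That the primary test is invalid.** The planned model includes school and classroom levels, so the wrong rationale does not carry into the analysis.
- **That the pupil and classroom counts contradict each other.** Under Method of Randomization and Allocation Concealment the article says "This process would enable participation of about 96 classrooms in each cluster, including about 4,500 students overall". That describes what the process would allow; 4,200 is a target. The figures are marked as approximate, and 4,500/192 = 23.4 pupils per classroom fits the stated 23 to 25.
- **That non-consent and loss of pupils were ignored.** A condensed article may leave this to the full protocol.

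**Conclusion.** The point holds in this form. The type-I rationale is wrong as written, whatever the ICC. The factor of 2 is not tied to school size, and at about 210 pupils per school it covers a school-level ICC of at most about 0.0048. The stated 80% power is not delivered at either end of the effect range, even where the doubling covers clustering exactly: about 70% for a halving of prevalence and about 15% for a 20% reduction. The figures at ICC 0.01 and 0.02 are illustrations over an assumed range.

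The shortfall has two sources. One is the base sizes, which are precision sizes for a single proportion; the other, if the ICC is above 0.0048, is the clustering allowance. Correcting the ICC alone would not repair the calculation. These results assume 3.8% control prevalence, equal school sizes, two-sided alpha 0.05 and 18 df.

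School recruitment and the endpoint assessment were completed in 2019, according to Trial Status, so this is now a matter of correct reporting and interpretation.

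**What to change.** 1. Delete the statement that the doubling limits type-I error. Say that inflation for clustering serves power and that the multilevel model controls type-I error.
2. Restate the calculation as a two-arm comparison (about 2,400 pupils for a 1.9-point reduction and about 16,100 for 0.8 points, before clustering), with design effect 1 + (m−1) × ICC at school level and m about 210.
3. Report the power or the detectable reduction that 20 schools and about 4,200 pupils give over a stated ICC range, for example 0.005 to 0.02, or at an ICC estimated from existing Sociescuela data or the trial's baseline data. Use t-based inference with 18 df.
4. Label this as a retrospective precision statement, so that it does not replace the record of how the size was originally set.

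The cost is a few sentences and a small table, with no extra enrolment and no change to the planned model. The downside is that the stated power becomes less favourable.
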